## Abstract

**Background:**

To mitigate the risk of stent thrombosis, patients treated by percutaneous coronary intervention (PCI) are administered dual anti-platelet therapy comprising aspirin and a platelet P2Y_12_ receptor inhibitor. Clopidogrel is a prodrug requiring activation by the cytochrome P450 enzyme, CYP2C19. In Saudi Arabia, it has been reported that approximately 26% of the population carries *CYP2C19*2* and/or *3 loss-of-function polymorphisms in addition to a high prevalence of CVD.

**Methods:**

This prospective (April 2013–December 2020) parallel assignment clinical trial focuses on ST-Elevation Myocardial Infarction (STEMI) patient outcomes. The clinical trial includes 1500 STEMI patients from two hospitals in the Eastern Province of Saudi Arabia. Patients are assigned to one of two groups; the control arm receives conventional therapy with clopidogrel, while in the active arm the Spartan RX CYP2C19 assay is used to determine the *2 genotype. Carriers of a CYP2C19*2 loss-of-function allele receive prasugrel or ticagrelor, while non-carriers are treated with clopidogrel. Follow-up is one year after primary PCI. The primary end point is the number of patients who develop an adverse major cardiovascular event, including recurrent MI, non-fatal stroke, cardiovascular death, or major bleeding one year after PCI.

**Discussion:**

The risk of stent thrombosis in PCI patients is usually reduced by dual anti-platelet therapy, comprising aspirin and a P2Y12 inhibitor, such as clopidogrel. However, clopidogrel requires activation by the cytochrome P450 enzyme, CYP2C19. Approximately 20% of the population are unable to activate clopidogrel as they possess the *CYP2C19*2* loss-of function (LoF) allele. The primary goal of this trial is to study the benefits of treating only those patients that cannot activate clopidogrel with an alternative that has shown to be a more effective platelet inhibitor and does not require bioactivation by the cytochrome P450 enzyme. We expect an improvement in net clinical benefit outcome in the active arm patients, thus supporting pharmacogenetic testing in PCI patients post STEMI.

**Trial registration:**

Trial registration name is “Bedside Testing of *CYP2C19* Gene for Treatment of Patients with PCI with Antiplatelet Therapy” (number NCT01823185) retrospectively registered with clinicaltrials.gov on April 4, 2013. This trial is currently at the patient recruitment stage.

## Introduction

### Background and rationale {6a}

Stent thrombosis is a common complication of PCI with stent implantation and is associated with STEMI [1, 2]. Patients with STEMI, who have been treated with stent implantation, are commonly treated with dual antiplatelet therapy (DAPT), such as clopidogrel and acetylsalicylic acid, to prevent atherothrombotic complications [2]. Worldwide, there are over 3 million people who suffer from STEMI every year [3]. The prodrug clopidogrel is converted into its active metabolite by Cytochrome P2C19 (CYP2C19) in the liver [4]. The P2Y12 receptors on platelets are inhibited by the active metabolites, which consequently leads to inhibition of platelet aggregation. Until recently, clopidogrel was the standard P2Y12 receptor inhibitor used to treat these patients. However, approximately 26% of the Saudi population carry polymorphisms in the *CYP2C19* gene which leads to the production of an inactive enzyme [5]. Patients with a *CYP2C19*2* LoF allele are unable to activate clopidogrel, as evidenced in numerous reports on drug platelet reactivity assays [6]. Studies have shown that patients who carry *CYP2C19**2 LoF alleles have a higher risk of developing atherothrombotic complications after stent implantation compared to non-carriers [7, 8].

During the last decade two novel antiplatelet drugs, namely prasugrel and ticagrelor, have come onto the market for clinical use [9]. Similar to clopidogrel, prasugrel irreversibly inhibits the P2Y12 receptor. However, unlike clopidogrel, prasugrel does not require bioactivation by the *CYP2C19* allele to act as an inhibitor of platelet aggregation [10, 11]. Moreover, ticagrelor, which is not a prodrug, directly inhibits the P2Y12 receptor [12]. There are some advantages for patients who are prescribed prasugrel and ticagrelor in that there is no interpatient variation of effectiveness and these drugs are faster-acting, which is especially important for patients with acute STEMI [13]. It has been shown that there is a significant decrease in the mortality rate in patients treated with ticagrelor compared to those patients who are treated with clopidogrel. Moreover, the influence of CYP2C19 on the action of these drugs is minimal [14]. However, clopidogrel remains the anti-platelet pharmaceutical of choice in Saudi Arabia due to its considerably lower cost and availability. In Saudi Arabia, it has been reported that approximately 26% of the population carries CYP2C19*2 and/or *3 loss-of-function polymorphisms in addition to a high prevalence of cardiovascular disease [15–21]. The primary and secondary objectives of the trial are shown below:

### Objectives {7}

#### Primary objectives of the trial

Despite a wealth of in vitro and retrospective findings that clopidogrel’s anti-platelet function is severely or completely absent in patients harboring the *2 allele of the *CYP2C19* gene, a prospective clinical trial is needed. The focus of this study is on patient outcomes to unequivocally establish the benefits of treating only those patients who cannot activate clopidogrel with more costly alternatives. However, these alternatives may impose a potentially higher risk for bleeding events. Our current prospective parallel assignment trial, which is the first multicenter pharmacogenetics Randomized Controlled Trial (RCT) in the field of personalized cardiovascular medicine in the Middle East, aims to study the benefits of treating only those STEMI patients that cannot activate clopidogrel with more costly alternatives that have shown to be more effective in platelet inhibition which will lead to reduced events but with a higher bleeding risk. Therefore, the objective of this study is to assess the efficacy, complication free survival, safety and cost-effectiveness of the CYP2C19 genotype guided antiplatelet treatment strategy, using clopidogrel or prasugrel/ ticagrelor. The primary outcomes are the numbers of patients in the groups who develop an adverse major cardiovascular event within one-year post PCI, including:
Recurrent MINon-fatal strokeCardiovascular deathPLATO major bleeding

#### Secondary objectives of the trial

The secondary objectives of the trial are to:
Study the cost-effectiveness of using *CYP2C19* genotype-guided antiplatelet therapyStudy the effect of genotyping strategy on individual outcomes of composite endpointAssess the quality of life of patients on alternative therapy

The secondary outcomes within one-year post PCI include:
Cardiovascular deathCerebrovascular deathDeath from recurrent MIStrokeStent thrombosisTarget vessel revascularizationCombination of the above

### Trial design {8}

This is the first multicenter RCT in the field of personalized cardiovascular medicine in the Middle East and aims to prove the value of bedside pharmacogenetic testing in approximately 1500 STEMI patients undergoing PCI. This study is a prospective parallel assignment trial, the aim of which is to determine whether prescribing prasugrel or ticagrelor, rather than clopidogrel, after primary PCI in carriers of *CYP2C19**2 LoF alleles is superior in reducing a net clinical benefit outcome consisting of cardiovascular death, myocardial infarction (MI), stent thrombosis, stroke and Platelet Inhibition and Patient Outcomes (PLATO) major bleeding. All patients aged between 18 and 70 years are eligible for inclusion. The sample size calculation is based on the estimated event rates for the primary net clinical benefit endpoint. The estimated event rate of the active arm is 9%, based on the recently published Patient Outcomes after primary PCI (POPular Genetics) trial and the Saudi Acute Myocardial Infarction Registry (STARS) [15–21]. The estimated event rate for the control arm is 13.6%, based on the PLATO trial [19, 20]. Using a power of 80% and an alpha level of 0.05, 1484 patients are required. Accounting for drop-outs 1500 patients will be included. Data are entered on http://www.openclinica.nl.

ST-segment elevation MI is defined according to the European Society of Cardiology and American College of Cardiology guidelines [8]. All demographic and clinical data are obtained for each participating patient from the medical records at the time of the index PCI. The treating physicians are not blinded to group allocation since the therapy could require alteration in patients with *CYP2C19*2* LoF alleles.

The Spartan RX device is being used to determine the *2 genotype of patients. The Spartan RX *CYP2C19*2* platform is placed in the catheterization lab of each hospital to enable immediate genetic testing. The trial was conducted in accordance with SPIRIT guidelines.

## Methods: participants, interventions and outcomes

### Study setting {9}

This study is being conducted in two major hospitals in the Eastern Province of Saudi Arabia, namely King Fahd Hospital of the University (https://www.iau.edu.sa/en/university-hospitals/king-fahd-hospital-of-the-university) and King Fahd Military Medical Complex (http://www.kfmmc.med.sa/Pages/Home.aspx) with King Fahd Hospital of the University acting as the center for data collection and analysis. These two major hospitals have cardiology departments with the facilities to perform PCI. Although it was anticipated that two other cardiac centers, namely Prince Sultan Cardiac center, King Fahd Hospital, Al Hofuf and Saud Al-Babtain Cardiac Center, Dammam Central Hospital, Dammam would join this trial, due to unforeseen reasons, these two centers are not able to participate.

Monitoring for major adverse cardiovascular events (MACE) continues for a period of one year after PCI. No difficulties have been encountered in *CYP2C19* genotyping in the catheterization laboratories in the two hospitals included in the study. The genotyping procedure was timed in both hospitals on the first 50 patients included in the study at each hospital. It took approximately 90–120 min to complete and submit the results to the treating cardiologist, thereby making this testing extremely feasible and practical in everyday clinical practice.

### Eligibility criteria {10}

The consultants involved in the project, who are all in the Department of Internal Medicine (Cardiology), perform the interventions. The inclusion and exclusion criteria are listed below:

#### Inclusion criteria

Patients aged between 18 and 70 years presenting with STEMI of more than 30 min and less than 12 hPatients eligible for PCI

#### Exclusion criteria

Life expectancy of less than one yearPreviously known genotypeReceiving chemotherapy for malignancyOn dialysis or receiving immunosuppressive therapy or have autoimmune diseaseHepatic impairmentHistory of bleeding diathesisReceiving vitamin K antagonist therapyConfirmed hypertension (hypertension is defined as office SBP values > 140 mmHg and/or diastolic BP (DBP) values > 90 mmHg or taken hypertensive medications)Out of normal range platelet count (any platelet count below 150 × 10^9^/L or above 400 × 10^9^/L)History of major surgerySevere trauma or fracturePregnancy and lactationConcomitant use of simvastatin, cytochrome P450 3A4 inhibitors or inducersHypersensitivity to clopidogrel, prasugrel or ticagrelor

### Who will take informed consent? {26a}

The attending physician obtains a signed written informed consent form from each participating patient prior to inclusion in the study.

### Additional consent provisions for collection and use of participant data and biological specimens {26b}

Not applicable.

## Interventions

### Explanation for the choice of comparators {6b}

#### Active comparator: Clopidogrel

*CYP2C19* genotyping will be carried out at the end of the study period. DNA is extracted from the collected blood samples and stored at − 80 °C. Genotyping will be conducted using the Spartan RX device. Clopidogrel is being used for treatment for one year according to local protocol. Clopidogrel is the standard of care in Saudi Arabia due to wider availability and lower costs. Patients receive clopidogrel 75 mg per day.

#### Intervention group: Clopidogrel

Genotyping is carried out using the Spartan RX device on all patients in the intervention group and those patients who do not carry the *CYP2C19*2* and/or *3 allele are given clopidogrel (75 mg per day).

#### Intervention group: Ticagrelor or prasugrel

Patients who carry the *CYP2C19*2* and/or *3 allele are prescribed prasugrel (10 mg once daily or 5 mg once daily if the patient older than 75 years or a body weight < 60 kg) or ticagrelor (90 mg twice daily) according to local protocol.

#### Intervention description {11a}

Buccal swabs are obtained from all subjects in the active arm for genotyping. Patients are genotyped for the CYP2C19*2 allele using the Spartan RX device. Carriers of the CYP2C19*2 allele receive either prasugrel (5 or 10 mg of daily depending on the patient’s age or weight once daily) or ticagrelor (90 mg twice daily). Non-carriers in the active arm are treated with clopidogrel (75 mg once daily) (Fig. 1). If patients have a history of stroke, ticagrelor is prescribed. As both prasugrel and ticagrelor are available in both hospitals, the choice of prescribed drug is according to the individual hospital’s protocol and the decision of the treating cardiologist. Patients whose therapy changes from clopidogrel to prasugrel or ticagrelor first receive a loading dose as part of the protocol in both hospitals unless the treating cardiologist decides otherwise. To validate the results, 10% of the samples collected will be genotyped using TaqMan StepOnePlus Assay at the Institute of Research and Medical Consultation at Imam Abdulrahman bin Faisal University. All collected blood samples will be disposed of once the genotype has been determined.

**Fig. 1 Fig1:**
[figure not shown]
Trial Schematic

### Criteria for discontinuing or modifying allocated interventions {11b}

Treatment with a P2Y12 inhibitor is standard care and is continued until the end of follow-up. Switching between P2Y12 inhibitors or early discontinuation is at the discretion of the treating physician. A patient is excluded from the study if he or she requests this or if the patient relocates to another region of Saudi Arabia as this prevents the patient from being followed up.

### Strategies to improve adherence to interventions {11c}

Not applicable.

### Relevant concomitant care permitted or prohibited during the trial {11d}

The local protocol for the treatment of patients is followed in both hospitals. On arrival at the hospital, patients are treated with a loading dose of DAPT (Aspegic 500 mg IV plus 600 mg clopidogrel). The type of stent used depends on the hospital’s availability and the discretion of the treating physician. The choice of site for catheterization, either through the femoral or radial site, is at the discretion of the treating physician. Antithrombotic agents used during PCI to minimize intraprocedural and stent-related thrombotic events are also used at the discretion of the treating physician. Patients in both arms receive 80 mg of acetylsalicylic acid in addition to the P2Y12 inhibitor (Fig. 1). Concomitant use of any other drugs by the patients is left to the discretion of the treating cardiologist.

### Provisions for post-trial care {30}

Not Applicable.

#### Outcomes {12}

The primary end point is the number of patients who develop an adverse major cardiovascular event which includes recurrent MI, non-fatal stroke, cardiovascular death, and PLATO major bleeding one-year post PCI. The definition of cardiovascular death, MI and stroke are as reported by Hicks et al., (2017) Cardiovascular and Stroke Endpoint Definitions for Clinical Trials [22]. Secondary outcomes within one-year post PCI include cardiovascular death, cerebrovascular death, death from recurrent MI, stroke, stent thrombosis, target vessel revascularization or a combination of the above.

#### Participant timeline {13}

Figure 2 Timeline and Milestones

**Fig. 2 Fig2:**
[figure not shown]
Timeline and Milestone

#### Sample size {14}

The sample size calculation is based on the estimated event rates for the primary net clinical benefit endpoint. The estimated event rate of the active arm is 9%, based on the recently published Patient Outcomes after primary PCI (POPular Genetics) trial and the Saudi Acute Myocardial Infarction Registry (STARS) [15–21]. The estimated event rate for the control arm is 13.6%, based on the PLATO trial [23, 24]. Using a power of 80% and an alpha level of 0.05, it is estimated 1484 patients are required to prove superiority of the genotype-guided strategy. Accounting from drop outs, 1500 patients will be included. Data are entered on http://www.openclinica.nl.

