### Assignment of interventions: allocation

#### Sequence generation {16a}

In both hospitals participating in the trial, all patients are randomly allocated to either the control arm or the active arm, as shown in Fig. 1. Randomization is computer generated in the cath labs of each hospital.

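### The stated 80% power is for a 4.6-point whole-arm difference, but only the 20–26% of patients who carry the allele are treated differently, so carriers would need an 18–23 point absolute risk reduction

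*Protocol article*

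**What the plan says.** Trial design {8} and Sample size {14} give the same calculation. The control rate of 13.6% is attributed to the PLATO trial. The active rate of 9% is attributed to the POPular Genetics trial and the Saudi registry. The conclusion is "Using a power of 80% and an alpha level of 0.05, it is estimated 1484 patients are required to prove superiority", followed by "Accounting from drop outs, 1500 patients will be included". Neither section mentions the share of carriers or gives a carrier-specific rate.

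On treatment, the Abstract says of the active arm: "Carriers of a CYP2C19*2 loss-of-function allele receive prasugrel or ticagrelor, while non-carriers are treated with clopidogrel". The comparator section {6b} gives every control patient clopidogrel 75 mg daily. Intervention description {11a} gives active-arm non-carriers the same daily dose. On allocation, {16a} says "all patients are randomly allocated to either the control arm or the active arm", and {20a} analyses everyone by intention to treat.

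On prevalence, Background and rationale {6a} says that in Saudi Arabia "approximately 26% of the population carries CYP2C19*2 and/or *3 loss-of-function polymorphisms". The Discussion part of the Abstract says "Approximately 20% of the population are unable to activate clopidogrel", referring to the *2 allele and naming no country.

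**The concern.** A genotype-guided strategy compared with uniform clopidogrel is a diluted comparison. Between 74% and 80% of patients are planned to take the same drug whichever arm they are in, so they add events and variance but no expected difference. A sample size for this design has to start from the carrier share and the effect in carriers. This one starts from two whole-arm rates taken from separate outside sources, so their 4.6-point gap is not an effect observed within one population.

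What is at stake is how the result will be read. Objectives {7} aims to settle the benefit of selective treatment unequivocally. If the true carrier effect is moderate, the likely outcome is a non-significant result, and the label of 80% power would present it as evidence against genotype guidance.

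**Working it through.** **Inputs.** Control 13.6%, active 9%, alpha 0.05, power 80%, N = 1484, rising to 1500 (Sample size {14}). Carrier share q = 0.26 ({6a}) or 0.20 (Abstract, Discussion). Sidedness and allocation ratio are not stated; two-sided and 1:1 are assumed because they reproduce N.

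**1. The plan's own figure.** Pooled two-proportion formula, with mean rate 0.113:

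n = [1.96·√(2·0.113·0.887) + 0.842·√(0.136·0.864 + 0.09·0.91)]² / 0.046² = 742.4 per arm.

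This matches 1484 (2 × 742). Power is 80.0% at 742 per arm and 80.4% at 750. The arithmetic is right for its inputs.

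**2. Dilution.** Let r be the non-carrier rate on clopidogrel, c the carrier rate on clopidogrel and a the carrier rate on the alternative drug.

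- Control arm: (1 − q)r + qc
- Active arm: (1 − q)r + qa
- Difference: q(c − a)

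Setting the difference to 0.046:

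- q = 0.26: c − a = 0.046/0.26 = 17.7 points
- q = 0.20: c − a = 0.046/0.20 = 23.0 points

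**3. Is that attainable?** Both values exceed the whole control rate. If carriers shared the 13.6% rate, preventing every carrier event would lower the arm rate by only 0.26 × 13.6 = 3.5 points (56% power with 750 per arm) or 0.20 × 13.6 = 2.7 points (36%).

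If instead the switch brings carriers exactly to the non-carrier rate (a = r), the active-arm rate equals r, so r = 9% and:

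- q = 0.26: c = (0.136 − 0.74 × 0.09)/0.26 = 26.7%, a risk ratio of 26.7/9 = 3.0
- q = 0.20: c = (0.136 − 0.80 × 0.09)/0.20 = 32.0%, a risk ratio of 32.0/9 = 3.6

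The article gives no carrier rate that would support these values; {6a} says only that carriers are at higher risk.

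**4. Power under the same model.** Hold the control rate at 13.6% and assume a carrier risk ratio R. Then r = 0.136/[(1 − q) + qR] and the active-arm rate is r. With 750 per arm:

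| Assumed R | Power, 26% carriers | Power, 20% carriers |
|---|---|---|
| 1.5 | 15% | 11% |
| 2.0 | 38% | 26% |
| 2.5 | 63% | 46% |
| 3.0 | 81% | 65% |

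**5. Carriers-only reading.** Trial design {8} words its aim in terms of carriers. Reading 13.6% versus 9% as carrier rates does not help: 1500 patients contain about 300 to 390 carriers, and 150 to 195 per arm gives 24% to 30% power.

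**6. Drop-out (secondary).** The allowance is (1500 − 1484)/1500 = 1.07%. At the stated rates, an assumed 5% loss (1425 analysed) gives 78.4% power and an assumed 10% loss (1350) gives 76.2%.

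**The case against.** The strongest reply is that the power table is one scenario among several. Nothing in the article says that carriers on the alternatives end exactly at the rate of non-carriers on clopidogrel, and no risk ratio from 1.5 to 3.0 appears in it. Background {6a} reports lower mortality on ticagrelor than on clopidogrel in general, so carriers might do better than that. If they end 20% below the non-carrier rate (an assumption), power at 26% carriers rises to 25%, 52%, 75% and 89% for the same four risk ratios. This is a fair limit on the table, which should be labelled as illustrative. It does not restore 80% for risk ratios up to 2.5. It also leaves the 17.7 points untouched, since that figure needs no assumption about where carriers end up. There is a pull the other way too: Objectives {7} expects more bleeding on the alternatives, and major bleeding is part of the composite, so the ischaemic benefit would have to be larger still.

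Second, the 20% figure names no country, so 26% is the better-supported value and about 18 points the better-supported requirement. That stands as a matter of emphasis. However, the 26% counts *2 and/or *3, while Trial design {8} and Intervention description {11a} describe testing for *2, so a lower share is not excluded.

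Third, the drop-out point is small. Retention {18b} plans to ask withdrawn participants for permission to use their data, and {18a} lets events be taken from medical records. Losses through relocation, request or side effects ({11b}, {22}) therefore need not all become missing outcomes. This is accepted, and the main conclusion does not rest on it.

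Finally, type I error and the intention-to-treat comparison are unaffected. That is true; the fault lies in the power claim.

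**Conclusion.** The concern holds. The 1484 is correctly computed from inputs that do not describe this trial. The design has 80% power only if switching removes about 17.7 points of absolute risk in carriers at 26% prevalence, or 23.0 points at 20%.

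This rests on no arm difference in non-carriers, which follows from the identical clopidogrel regimen, and on adherence to the assigned strategy. Switching at the physician's discretion ({11b}) would usually raise the requirement. The result is not sensitive to the control rate: with 750 per arm, an assumed 10% control rate needs 15 to 20 points in carriers and an assumed 20% needs 21 to 27.

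The power values for particular risk ratios (15% to 81% at 26% carriers, 11% to 65% at 20%) depend on the further assumption that the carrier excess is fully removed. The unqualified 80% should not stand.

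**What to change.** In both Trial design {8} and Sample size {14}:

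- Build the two arm rates from four stated quantities: carrier prevalence, the non-carrier rate on clopidogrel, the carrier rate on clopidogrel and the carrier rate on the alternative drugs. Give a source or a labelled assumption for each.
- State the carrier effect that 9% versus 13.6% implies: 17.7 points at 26% prevalence, with 23.0 points at 20% as a sensitivity value.
- Replace the flat 80% with power over a range of carrier risk ratios, and say what is assumed about carriers' risk after the switch.
- State that 1500 covers a 1.07% loss, and give power at 5% and 10% loss.

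The cost is a restated figure that looks less favourable. No added enrolment, data collection or change of analysis is proposed.
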